## Abstract

Background: The most recent evidence has shown that the pandemic of COVID-19 caused an increasing problem with spinal pain in the population of teenagers and young adults. This may be explained by prolonged sitting times in flexed positions with electronic devices. Positions maintained for a prolonged time cause overloading of soft tissue and discogenic symptoms. This study aims to evaluate the effectiveness of the active break program in reducing musculoskeletal discomfort and LBP (low back pain) among young people. Methods: This will be a randomized controlled study. The participants will be recruited from Bachelor’s course students of the Physical Education Department aged 18–25 years. The participants will be assigned to an experimental group (with an active break) and a control group. The group with an active break with lumbar and hip extension exercises will be recommended to take a break for every 30 min of sitting. The control group will receive self-care recommendations. The primary outcomes will be pain intensity (Visual Analogue Scale), disability index (Oswestry Disability Index), and perceived musculoskeletal discomfort during prolonged sitting (Borg scale), assessed at baseline and after the intervention, and the Global Perceived Effect, only assessed after the 12-week intervention. The secondary outcome will be a Post-Intervention Questionnaire (a 5-item self-completed questionnaire), only assessed after the 12-week intervention. Results: Our main research outcome—exercise protocols and interventions—will lead to the development of recommendations and protocols for the LBP population. It is important to determine the effect of interventions that are feasible and effective in addressing LBP and perceived musculoskeletal discomfort in young people. Conclusions: This is the first study examining the effect of active breaks with proposed lumbar and hip extension exercises on reducing or decreasing LBP in students based on a search of the literature. Exercises and recommendations will be the basis for developing proprietary preventative and therapeutic programs, which will be implemented in selected educational institutions.

## 1. Background

According to the World Health Organization (WHO), between 60 and 85% of the world’s people—in both developed and developing countries—lead a sedentary lifestyle, making it one of the major but under-resolved public health problems of our time [1]. The most recent evidence has also shown that the situation relating to the COVID-19 pandemic has adversely affected the health of the entire world population [2,3,4,5]. During the COVID-19 pandemic, many countries switched their teaching programs to e-learning, where students spent long hours using electronic devices [6]. E-learning, and thus prolonged sitting, is a topic that returned to higher education at the beginning of the 2022–2023 academic year. However, this change in learning methods is associated with musculoskeletal dysfunction including low back pain (LBP) [6,7].

LBP was one of the most common musculoskeletal disorders in the pre-pandemic period [8,9,10,11] and today it is known that the COVID-19 pandemic has increased the prevalence and intensity of LBP [6,7,10]. It should be emphasized the problem of LBP does not only apply to adults and the elderly. Teenagers and even children are increasingly struggling with serious back pain [9]. In the younger generation, this may be explained by sedentary behavior, prolonged sitting time, next to a reduced level of physical activity. The most common sedentary behavior, especially among adolescents, is the time spent sitting watching television, using the computer, playing video games, and using a smartphone [12].

Physical activity is significant for preventing LBP [13]. On the other hand, physical load during daily activities at work and during leisure time are defined as risk factors for LBP [14,15]. Exposure to physical load is not limited to one specific back-threatening activity but encompasses a compilation of activities, such as flexion, rotation, lifting, carrying, and pulling. Many popular exercises and positions with lumbar flexion may cause significant compression of the spine [16]. Prolonged sitting has been identified as a risk factor for LBP [17]. In most people, a relaxed sitting position is characterized by a loss of lumbar lordosis and a kyphotic position of the entire spine [18,19,20]. Such a position in the long-term results in several negative consequences within the musculoskeletal system. Prolonged sitting causes stretching of the supraspinous ligaments and a decrease in the activity of the multifidus muscle, which leads to limitations in its protective function for the spine. The load on the lumbar spine in the sitting position is significant. Disabling the proprioceptive function causes the load to be transferred to passive structures, such as ligaments and intervertebral discs, or passive muscle properties [21,22]. In addition, Williams et al. [23] showed that a kyphotic posture results in more back pain than a lordotic posture.

Re-education on sitting posture is a common aspect of LBP management. Physiotherapists recommend many different sitting positions to prevent and treat the negative effects of prolonged sitting. However, there is debate regarding what is an optimal sitting posture [18,24,25]. Studies showed that sitting posture with the backrest on the chair induced minimal changes in lumbar lordosis and significantly lesser pain compared to other types of the chair [26,27,28]. Each sitting position causes a static load on the spine. Shifting the load to other tissues can be achieved with a change in position. Repositioning is recommended to minimize the risk of tissue overload [21]. The systematic review of Waongenngarm et al. [29] showed that active breaks with postural changes were found to be effective in reducing discomfort and pain. Nonetheless, they suggested that there is insufficient real-life evidence (workplace contextualized) to provide more detailed information about the type of breaks and the break protocol [29]. On the other hand, others have investigated the effects of breaks on discomfort or pain in people at risk of LBP and excluded participants with LBP who reported pain in the last few months [29,30].

Investigations into the prevention and treatment of early symptoms of back pain are also worthwhile from an economic perspective because the direct costs of the treatment of individuals with chronic and recurrent LBP are high [31,32]. Therefore, it is very important to prepare evidence-based ergonomic recommendations—exercise protocols and interventions—for young people to reduce LBP and musculoskeletal discomfort during prolonged sitting, and consequently, to maintain health and quality of life. To our knowledge, these problems have not been fully investigated, especially among young people with LBP.

The study aims to evaluate the effectiveness of the active break program in reducing LBP and perceived musculoskeletal discomfort during prolonged sitting in young people with LBP.

## 2. Methods

This study will be a randomized controlled trial. The protocol was developed by the Recommendations for Randomized Trials (SPIRIT, Standard Protocol Items) [33]. Results will be reported as stated in the Consolidated Standards of Reporting Trials (CONSORT) statement [34]. This study is being conducted at the Faculty of Physical Education and Health, Jozef Pilsudski University of Physical Education in Warsaw, Biala Podlaska, Poland. The study was registered on clinicaltrials.org [NCT05810519] and complies with the latest version of the Helsinki Declaration [35]. This study was approved by the Ethics Committee of the AWF Warsaw [SKE 01-05/2023]. Written informed consent for participation will be obtained from the students.

### 2.1. Study Population

This study will include 1st- and 2nd-year students of a Bachelor’s course in Physical Education. Detailed information about participants will be given in the eligibility criteria.

#### 2.1.1. Inclusion Criteria

Participants will be recruited according to the inclusion criteria: female and male; age between 18 and 25 years; experiencing non-specific LBP (defined as pain and discomfort localized below the costal margin and above the inferior gluteal folds), without radiation to legs; not using medication for low back pain in the last 3 months; not having a surgical history due to spinal problems; not having radiculopathy or other injuries such as fractures, stenosis or tumors in the spine; lack of any treatment related to the low back within the last 6 months.

#### 2.1.2. Exclusion Criteria

Participants will be excluded from this study if they experience a level of low back pain of at least 7 on the 0–10 Visual Analogue Scale (VAS) scale (where 0 and 10 are “no pain” and “most severe pain I can imagine”, respectively); spinal pathology (e.g., tumor, infection, fracture, inflammatory disease); pregnancy; nerve root compromise; previous spinal surgery; major surgery scheduled during treatment or follow-up period; disc herniation; leg length discrepancy; pelvic asymmetry; and presence of any contraindication to exercise. In order to achieve homogeneity in terms of physical activity, professional athletes will be also considered ineligible.

### 2.2. Assessment

Before the assessment, written consent will be obtained from the participants. A blinded assessor, who is a physiotherapist with five years of clinical experience, will evaluate the eligibility criteria. The baseline assessment will be conducted before the random distribution of the participants into the groups. The assessment of the outcomes will be collected at baseline and immediately after the 12-week intervention.

### 2.3. Pre-Intervention Questionnaire

The survey contained questions regarding:-gender,-age,-current physical activity (sports discipline, number of training days and hours per week),-illnesses, injuries, surgical history due to spinal problems, treatment related to LBP, diagnosed defects in body posture,-experience of LBP within the last three months. Individuals who respond positively (“yes”) to the question “Have you experienced low back pain for the last three months?” will then answer the question in the frequency of experiencing LBP (rarely, few times per week, often, or constantly) and the types of situations in which LBP occurred or increased.

### 2.4. Outcome Measures

The primary outcomes will be the frequency of LBP (questionnaire), pain intensity (VAS), disability index (ODI) and perceived musculoskeletal discomfort during prolonged sitting (Borg scale), assessed at baseline and after the 12-week intervention, and the Global Perceived Effect (7-point Likert scale), assessed only after the 12-week intervention. The secondary outcome will be the Post-Intervention Questionnaire (5-item self-completed questionnaire), assessed only after the 12-week intervention. Table 1 shows the distribution of the different measures across the time points during the present study.

All the tests will be performed during morning hours in the laboratory room at the Regional Centre for Research and Development in Biala Podlaska.

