#### 2.5.3. Perceived Musculoskeletal Discomfort during Prolonged Sitting

Perceived musculoskeletal discomfort during prolonged sitting will be measured using the Borg CR-10 scale during 1 h of sitting [40]. The body regions (i.e., the neck, shoulder, elbow, wrist, upper back, low back, buttocks, hip/thigh, knee, and ankle) will be defined according to a body chart from a modified Nordic questionnaire [41]. Participants will indicate which parts of their body experienced musculoskeletal discomfort and how much discomfort was felt (on a scale of 0–10; 0 denotes no discomfort and 10 denotes extreme discomfort).

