### 2.11. Study Procedures

#### 2.11.1. Sample Size

The sample size was determined using the software G*Power 3.1, which used Factorial ANOVA with assumption of a medium-sized effect (d = 0.50) at a significance level of 0.05 and statistical power of 0.85. Therefore, the required sample size for this study will be 50 participants randomly assigned in two different groups. The sample will be increased by 20% to compensate for possible dropouts, leading to 32 individuals in each group (overall sample = 64 participants).

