### 3.1. Statistical Analysis

The data will be analyzed using Statistica 14.0.0.15 program (TIBCO Software Inc., Palo Alto, CA, USA, 2020). The parameters will be described using basic descriptive statistical measurements, i.e., the percentage for qualitative variables, and the mean and standard deviation for quantitative variables. For variables that do not meet the criteria of normality of distribution, data will be presented as medians and quartile ranges. The normality of the distributions of the quantitative variables under study will be tested using the Shapiro–Wilk test. To verify the homogeneity of variances, Lavene’s test will be conducted. The chi-square test will be used for categorical variables. Descriptive statistics will be calculated separately for all groups (active break vs. control). The Student’s *t*-test (if data meet the criteria of normality of distribution) and the Mann–Whitney U test (if data do not meet the criteria of normality of distribution) will be used to compare parameter values between groups (active break vs. control). The Wilcoxon signed rank test will be used to examine the differences in parameters (VAS, ODI and discomfort) before and after the intervention. Intention-to-treat analysis will include all randomized patients. The significance level will be set at *p* < 0.05.

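### Four or five co-equal primary outcomes share one flat 0.05 level with no success rule, so an any-one-counts claim carries a false positive risk of about 13-23%, not 5%

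*Protocol article*

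**What the plan says.** **Which outcomes are primary.** Section 2.4 reads: "The primary outcomes will be the frequency of LBP (questionnaire), pain intensity (VAS), disability index (ODI) and perceived musculoskeletal discomfort", and continues "and the Global Perceived Effect (7-point Likert scale), assessed only after the 12-week intervention". That makes five. The Abstract begins its list differently: "The primary outcomes will be pain intensity (Visual Analogue Scale), disability index (Oswestry Disability Index), and perceived musculoskeletal discomfort during prolonged sitting (Borg scale", then adds the GPE. That makes four, without LBP frequency. Sections 2.5.1 to 2.5.4, under the primary outcome heading, define the same four, and Table 1 schedules only those four plus the secondary questionnaire. Elsewhere LBP frequency appears as a questionnaire item (sections 2.3 and 2.10) and a stratification factor (section 2.11.2).

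**What is scored for discomfort.** Section 2.5.3 lists ten regions: "the neck, shoulder, elbow, wrist, upper back, low back, buttocks, hip/thigh, knee, and ankle". It says "Participants will indicate which parts of their body experienced musculoskeletal discomfort and how much discomfort was felt". It names no total, maximum or key region.

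**What error rule applies.** Section 3.1 provides for between-group t-tests or Mann-Whitney tests and for chi-square tests. Its only error rule is the sentence that begins "The significance level will be set at", which gives 0.05. Section 2.11.1 sizes the trial "at a significance level of 0.05 and statistical power of 0.85" for one generic effect (d = 0.50) that is tied to no named outcome.

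**The concern.** A 5% level protects a trial's conclusion when that conclusion rests on one test, or on several tests bound by a rule. Here several outcomes rank equally and no rule links them. A report could therefore call the trial positive on whichever primary crosses 0.05, and the chance that at least one does so under no effect exceeds 5%.

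Two features make this worse. The article disagrees with itself on whether LBP frequency is primary, so the size of the family is not settled. And the Borg outcome has no defined analysis score, so a total, a maximum or a single region could be chosen after the data are seen. The results are meant to support recommendations for educational institutions, so the reliability of the headline claim matters.

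**Working it through.** **Inputs from the article**
- Primary outcomes: k = 5 (section 2.4) or k = 4 (Abstract, sections 2.5.1-2.5.4, Table 1).
- Level: 0.05 (section 3.1).
- Discomfort regions: 10 (section 2.5.3).

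**Assumptions, because the article is silent**
- Tests are two-sided.
- Any one significant primary counts as success.
- All pairs of outcomes have the same correlation, shown from 0 to 0.8.
- No true effect on any outcome.

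The article states no familywise error rate to reproduce. Its only stated error rate is the flat 0.05.

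**Independent tests.** Familywise error = 1 − (1 − 0.05)^k:
- k = 4: 1 − 0.95^4 = 1 − 0.8145 = 18.5%
- k = 5: 1 − 0.95^5 = 1 − 0.7738 = 22.6%

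**Correlated tests.** One million draws of equicorrelated standard normals, counting a draw when any |Z| exceeds 1.96. The last column shows what would follow if all ten regions were tested separately alongside the other four outcomes of section 2.4 (4 + 10 = 14). The row for correlation 0 uses the formula.

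| Assumed correlation | 4 outcomes | 5 outcomes | 14 tests (conditional) |
|---|---|---|---|
| 0 | 18.5% | 22.6% | 51.2% |
| 0.3 | 17.4% | 21.0% | 43.8% |
| 0.5 | 15.6% | 18.3% | 34.9% |
| 0.7 | 13.0% | 14.8% | 24.8% |
| 0.8 | 11.4% | 12.7% | 19.7% |

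Even at a correlation of 0.8 the error is 11.4/5 = 2.3 times the nominal level for four outcomes and 12.7/5 = 2.5 times for five. The direction of the finding does not depend on the assumed correlation; its size does.

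The before-and-after Wilcoxon tests in section 3.1 are not counted here.

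**After the fix.** One primary outcome, or a fixed testing order, holds the error at 5%. Holm across the primaries also holds it at 5%; its first step uses 0.05/5 = 0.01 for five outcomes or 0.05/4 = 0.0125 for four.

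**The case against.** **The adjustment may be in the statistical analysis plan.** Adjustment methods and testing order are often left to that plan, which is not shown, and section 3.1 does not say in words that each test is unadjusted. This stands in part: the absence of an adjustment method is not by itself a finding. The point rests on what the article does fix: several primaries of equal rank, two conflicting lists of them, one flat level, and a sample size set at that level for a single generic effect.

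**No any-one rule is stated.** True, and neither is an all-must-succeed rule, under which there would be no inflation. The percentages are therefore conditional on the any-one reading. The text as written permits that reading.

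**The outcomes are correlated.** They probably are, and the table allows for it. The error falls but stays well above 5%.

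**A stronger reading is tempting.** A reader might infer that the primary family is really 14 tests, that the error is 51%, and that a chance result in the wrist or knee would count as primary success for a back pain programme. The article does not support this. Section 2.4 counts discomfort as one outcome, section 3.1 names it as one parameter, and no regional tests are planned. The 51% also needs all 14 tests to be independent, which is unlikely for ratings given by one person during the same hour of sitting. What stands is narrower: the analysed Borg score is undefined, so regional testing is left open.

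**Conclusion.** The concern holds. The article fixes co-equal primary outcomes, disagrees on whether there are four or five, and gives one 0.05 level without a rule for combining them. If any one significant primary counts as success, the familywise error is about 13-19% for four outcomes and 15-23% for five, for assumed correlations of 0.7 down to 0, against the stated 5%.

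The undefined Borg score is a second, related defect. If the ten regions were tested separately, the error would be about 25-44% at assumed correlations of 0.7 to 0.3. The 51% figure is only the independence bound and should not be quoted as the expected error.

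**What to change.** 1. **Reconcile the list.** State in the Abstract, sections 2.4 and 2.5, and Table 1 whether LBP frequency is a primary outcome.
2. **Set one rule for the primary claim.** There are two workable options:
   - Name one primary outcome at two-sided 0.05, with the others secondary in a fixed order or with Holm adjustment. VAS pain intensity is one candidate. Section 2.5.1 must first be reconciled, because it describes average pain and then asks for maximal pain over the last three months. Ranking VAS first is a choice for the sponsor, since the stated aim names both pain and sitting discomfort.
   - Keep the reconciled primaries and apply Holm across them.
3. **Define the Borg outcome.** Fix it as the low back region score and label the other nine regions exploratory.
4. **Restate the power** for the chosen outcome and alpha.

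**Cost.** Steps 1 to 3 need wording changes and an update of the registry entry, and no new measurements. Under the first option some outcomes lose primary status; under the second, they face a stricter level.

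Step 4 may be the larger cost, because section 2.11.1 ties its power to no outcome. For illustration, take a simple two-group t-test at d = 0.50 with 25 per group (50/2, before the dropout allowance). Power is about 41% at 0.05 and 19% at 0.01, and 85% power at 0.05 needs 73 per group. Whether 50 participants suffice under the factorial ANOVA the article cites is a separate question, but the power statement cannot stay unattached to an outcome and a level.

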### 2.5. Primary Outcome Measures

#### 2.5.1. Pain Intensity

Average pain intensity will be assessed with the VAS. VAS is a validated, objective and unidimensional measure of pain [36]. Participants will be asked to rate their maximal pain intensity from the last 3 months on a 10 cm line. The centimeters will be marked by the participants and will be measured and classified according to the following key: 0—no pain, 1–3—mild pain, 4–6—moderate pain and 7–10—severe pain [37].

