### 2.8. Active Break Program

The experimental group will receive recommendations to take an active break every 30 min of sitting for 12 weeks. In the experimental intervention, the active break program will include lumbar and hip extension exercises and will be based on self-education with an explanation of the importance of regular training. The participants will receive a booklet with photographed and described exercises. The education will be carried out by an experienced physiotherapist.

The habit of doing exercises during an active break will be formed gradually (Table 2). In the first month, participants will be instructed to perform the proposed exercises in a standing position with lumbar and hip extension every 30 mins or whenever musculoskeletal discomfort occurs. In the second month, the complexity of the active break exercises will be increased by progressing to spine hyperextension exercise. In the third month, participants will be instructed to also perform spine hyperextension exercise in a sitting position. The number of repetitions depends on the needs of the participants.

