## Figures and Tables

**Table 1 jcm-13-00612-t001:** SPIRIT table of enrolment, intervention, and assessment.

	Enrollment	Before Intervention	Randomization	Intervention
Timepoint	1st month	2nd month	2nd month	3rd, 4th, and 5th months (12 weeks)
Enrollment				
Eligibility pre-screening	+			
Informed consent	+			
Allocation			+	
Interventions				
Active break group and control group				+
Assessments				
Pain intensity		+		+
Disability index		+		+
Perceived musculoskeletal discomfort		+		+
The Global Perceived Effect				+
Post-Intervention Questionnaire				+

**Table 2 jcm-13-00612-t002:** Active break exercises.

	Exercises	Duration	
Phase 1—1st month	Spine extension in standing position: Extending arms above the head and reaching up. Straightening the torso until feeling the stretch in the lower spine. The range of arm extension depends on the mobility of the shoulder joints.	30 s	[figure not shown]
	2. Neutral standing position (lumbo-pelvic upright position)		[figure not shown]
	3. Neutral sitting position (lumbo-pelvic upright position)		[figure not shown]
Phase 2—2nd month	Spine extension in standing position: Standing facing forward, feet on the floor. Extending arms above the head and reaching up. Straightening the torso until feeling the stretch in the lower spine. The range of arm extension depends on the mobility of the shoulder joints.	45 s	[figure not shown]
	2. Spine hyperextension in standing position: Putting arms behind the neck and keeping together elbows. Performing head retraction (hyperextension) and tilting your head back until feeling the hyperextension in the lower spine. This exercise is intended for participants who do not experience discomfort or increase in back pain caused by hyperextension in the lumbar lordosis. Participants sensitive to hyperextension perform this exercise with lumbar extension.		[figure not shown]
	3. Neutral standing position (lumbo-pelvic upright position)		[figure not shown]
	4. Neutral sitting position (lumbo-pelvic upright position)		[figure not shown]

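### The primary VAS outcome is labelled average pain but asks for maximal pain over 3 months, a window that at week 12 spans the whole intervention

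*Protocol article*

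**What the plan says.** Section 2.4 makes VAS pain intensity one of several primary outcomes, "assessed at baseline and after the 12-week intervention, and the Global Perceived Effect" being measured only at the end. Section 2.5.1 opens its definition with "Average pain intensity will be assessed with the VAS" and then gives the instruction to participants: "Participants will be asked to rate their maximal pain intensity from the last 3 months on a 10 cm line". The centimetre reading is then sorted into none, mild, moderate and severe.

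On timing, section 2.2 says: "The assessment of the outcomes will be collected at baseline and immediately after the 12-week intervention". Section 2.10 repeats this. Table 1 places the intervention in the "3rd, 4th, and 5th months (12 weeks", so the article itself treats 12 weeks and three months as the same span. No separate recall period is given for the second rating.

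On the programme, section 2.8 says: "The habit of doing exercises during an active break will be formed gradually". Table 2 sets out three monthly phases.

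**The concern.** There are two linked problems.

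- **Construct.** Average and maximal pain are different quantities. A reader of the results could not tell which was compared, and the published label would not match the question asked.
- **Recall window.** A maximum is fixed by the single worst moment in its window. If the window is the treatment period itself, a participant with one bad day in week 1 and no pain by week 12 scores as though nothing improved. The programme is phased in, so the earliest weeks deliver the least of it but count fully towards the score.

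At stake is whether one of the primary outcomes can show pain after the intervention. The wording cannot be repaired in the analysis once the ratings are collected.

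**Working it through.** **1. The two definitions.** Section 2.5.1 names an average in its first sentence and asks for a maximum two sentences later. Sections 2.4, 2.10 and 3.1 refer only to pain intensity or the VAS and do not settle the matter. The contradiction needs no arithmetic.

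**2. The window.**
- Intervention: 12 × 7 = 84 days.
- Three calendar months: 3 × 365.25/12 = 91.3 days.
- Overlap: 84 of 84 treatment days. Read literally, the window also reaches 91.3 − 84 ≈ 7 days before the start. If three months means 12 weeks, as Table 1 has it, the overlap is exact with nothing before.

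**3. Consequence for power.** The article gives no VAS standard deviation, no effect in centimetres and no time course, so it has no figure of its own to reproduce here. The following is an illustration on assumed inputs. For participant i in week j,

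x_ij = u_i + e_ij − δ_j (active arm only), truncated to 0–10,

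with u_i ~ N(3, 1.2²), e_ij ~ N(0, 1.2²), and δ_j reaching 1 cm by week 12. There are 200,000 simulated participants per arm. The 12-week maximum is compared with the week-12 score. Power is from the noncentral t distribution at 32 per arm (section 2.11.1), two-sided 0.05, df = 62, noncentrality d × √(32/2) = 4d.

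| Assumed time course | d, 12-week maximum | d, last week | Power, maximum | Power, last week |
|---|---|---|---|---|
| Linear over 12 weeks | 0.34 | 0.58 | 0.27 | 0.63 |
| Linear, full by week 8 | 0.46 | 0.59 | 0.44 | 0.64 |
| Monthly 50, 75, 100% | 0.52 | 0.59 | 0.53 | 0.64 |
| Linear, full by week 4 | 0.60 | 0.59 | 0.66 | 0.64 |
| Full and constant from week 1 | 0.73 | 0.59 | 0.82 | 0.64 |

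For the first row, 4 × 0.34 = 1.36 gives power 0.27 and 4 × 0.58 = 2.32 gives 0.63. Repeat runs move d by about 0.01.

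The maximum has a smaller SD than a single week (about 1.38 against 1.58 cm). A modest loss in the raw difference therefore need not cost power.

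**4. Raw differences under other assumptions.** With weekly worst pain averaging 4 cm, between-person SD 1.2 and weekly SD 1.0 to 1.5, the maximum keeps the following share of the last-week difference:

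| Effect builds over | 12-week window | 13-week window (one pre-treatment week) |
|---|---|---|
| Immediate | about 1.0 | 0.84–0.88 |
| 4 weeks | 0.83–0.88 | 0.71–0.76 |
| 8 weeks | 0.63–0.66 | 0.54–0.60 |
| 12 weeks | 0.48–0.50 | 0.42–0.46 |

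**5. Infrequent pain.** Eligibility needs only a yes to low back pain in the last three months (section 2.10), and the frequency item starts at rarely (section 2.3). Suppose pain is present in half of weeks, independently, averaging 4 cm when present, with SDs of 1.2 and a 1 cm effect on intensity only. The maximum then gives d = 0.34 (12-week ramp) to 0.68 (constant), and the last-week score gives 0.23. With pain in 75% of weeks the figures are 0.35 to 0.71 against 0.35.

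**The case against.** The best defence is that worst pain over the treatment period, set against worst pain over the preceding three months, is a coherent matched comparison. It uses the same window as the eligibility question. The aim stated in the Background is to reduce low back pain and discomfort, without restriction to status at week 12. Other primary outcomes look at the end of treatment: discomfort during one hour of sitting, and the Global Perceived Effect, which asks about current status. Participants also exercise from the first month. By section 2.8 and Table 2, complexity and duration (30, 45, 60 s) increase while the 30-minute interval between breaks does not, so a near-zero effect in the first month is not something the article states.

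Much of this stands. A reader might infer that the 3-month maximum dilutes any effect and biases the pain result towards no difference. The documents do not support that: they give no time course, and the direction of the power effect changes with it (step 3). Nor do they show that a last-week rating is always better (step 5). A reader might also infer that the window reaches back before randomisation. That holds only if three months is taken as longer than the 12 weeks with which Table 1 equates it.

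The defence does not remove the conflict between average and maximal. It also does not make a maximum over the whole treatment period a measure of pain at its end.

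**Conclusion.** The point holds in a limited form and should be fixed. Two parts rest on the text alone: the primary VAS outcome has two incompatible definitions, and the week-12 recall window covers the entire intervention, so one early episode can determine the score.

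The loss of power is conditional. On the assumed inputs it is large if the effect builds over all 12 weeks (0.27 against 0.63) and moderate for monthly effects of 50, 75 and 100% (0.53 against 0.64). It is absent if the effect is complete within about 4 weeks, and reversed if the effect is immediate and constant. These figures rest on assumed means, SDs, a 1 cm effect and pain in every week, none of which the article supplies. They show how much the wording can matter; they do not estimate this trial's power.

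**What to change.** State one construct, average or worst pain, and use that term in the label, the item and the report. Use identical wording at baseline and week 12. Set a recall period short enough that the second rating reflects the late part of the intervention, for example the last 1 to 4 weeks; 4 weeks would roughly match the third phase in Table 2. Analyse the centimetre reading as a continuous score and keep the severity bands for description. The 3-month maximum can stay as a baseline or descriptive item.

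Correcting the label alone, so that the outcome is openly worst pain during the treatment period, would remove the contradiction. It would still not provide a measure of pain at the end of the intervention.

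The cost is one questionnaire item and one paragraph. The downside is that a very short window such as 7 days will give many zeros in participants with infrequent pain and may lower power, as step 5 shows. Choose the window with the baseline answers to the pain-frequency item in view, and before any outcome data are compared by group.
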